## Abstract

**Introduction:**

The burden of post-tuberculosis (TB) lung disease (PTBLD) is steadily increasing in sub-Saharan Africa, causing disability among TB survivors. Without effective medicines, the mainstay of PTBLD treatment evolves around disease prevention and supportive treatment. Pulmonary rehabilitation (PR), a low-cost, non-pharmacological intervention has shown effectiveness in a group of PTBLD individuals but has not been tested in a clinical trial. This study aims to assess the impact of a 6-week PR programme on maximal exercise capacity and other outcomes among adults in Uganda living with PTBLD.

**Methods and analysis:**

This is a randomised waiting-list controlled trial with blinded outcome measures, comparing PR versus usual care for patients with PTBLD. A total of 114 participants will be randomised (1:1) to receive either usual care (on the waiting list) or PR, with follow-up assessments at 6 weeks and 12 weeks postintervention. The primary outcome is change in walking distance measured by the Incremental Shuttle Walk Test from baseline to the end of 6 weeks of PR. All secondary outcomes will be compared between the PR and usual care arms from baseline to 6-week and 12-week follow-ups. Secondary outcomes include self-reported respiratory symptoms, physical activity, psychological well-being, health-related quality of life and cost–benefit analysis. All randomised participants will be included in the intention-to-treat analysis population. The primary efficacy analysis will be based on both per-protocol and modified intention-to-treat populations.

**Ethics and dissemination:**

The trial has received ethical clearance from the Mulago Hospital Research and Ethics Committee (MHREC 1478), Kampala, Uganda as well as the Uganda National Council for Science and Technology (SS 5105). Ethical approval has been obtained from the University of Leicester, UK research ethics committee (Ref No. 22349). Study findings will be published in appropriate peer-reviewed journals and disseminated at appropriate local, regional and international scientific meetings and conferences.

**Trial registration number:**

ISRCTN18256843.

**Protocol version:**

Version 1.0 July 2019.

Strengths and limitations of this studyThe study aims to determine the effectiveness of pulmonary rehabilitation (PR) for individuals with post-tuberculosis lung disease (PTBLD) in a clinical trial setting. To our knowledge, this is the first pragmatic, fully powered effectiveness trial for PR in PTBLD in Africa. This is a progression of previous work that established feasibility and acceptability of PR design for people living with PTBLD in Uganda.Due to funding limitations, we are unable to carry out a multi-site study. This may limit generalisability of the study findings.

## Introduction

### Background and rationale

In 2018, 24% of the global Tuberculosis (TB) incident cases occurred in the African region.^1^ Furthermore, 24 of the 30 high TB/HIV burden countries, including Uganda, are in the African region; accounting for 71% of the global burden of HIV associated TB.^1^ Despite great strides made over the recent years to achieve the 90% treatment success rate, as part of the ‘End TB strategy’ target,^1^ a significant number of TB survivors continue to have poor health-related quality of life (HRQoL).^2^ This may be attributed to the pulmonary function impairment following TB treatment, which has been reported in approximately 50% of pulmonary TB survivors.^3^ The reduction in ventilation and perfusion attributed to the permanent lung parenchymal damage^4^ clinically manifests as long-term respiratory symptoms and eventually chronic respiratory disease (CRD), including chronic obstructive pulmonary disease (COPD), bronchiectasis and aspergillosis.^5 6^

Adults with post-TB respiratory symptoms develop skeletal muscle dysfunction, related to physical inactivity and systemic inflammation, which is often compounded by impaired nutrition and poverty.^7^ Such patients enter a vicious cycle with falling body weight, progressive morbidity and increased mortality.^7^ Individuals affected by CRDs tend to avoid exercise and become increasingly deconditioned and demotivated, leading to a cycle of decline. There are no effective medicines for post-TB lung disease (PTBLD) and the mainstay of treatment evolves around disease prevention and supportive treatment. The disease, previously neglected by health services and researchers, is now the focus of increasing interest.^8 9^

In low-income and middle-income countries (LMIC) where healthcare focuses on treatment and prevention of infectious diseases, as opposed to managing chronic diseases, the care for adults living with CRD presents a major challenge. Consequently, patients that require long-term and systemic approaches often receive sub-optimal medical care, inevitably leading to preventable deaths in resource poor settings.

Pulmonary Rehabilitation (PR) is a low cost, high impact intervention that reverses the disability associated with CRDs, and is supported by the highest level of research evidence in high-income countries.^10 11^ A PR programme brings together health professionals from many disciplines offering supervised exercise training and disease education, supporting people to manage their own disease. However, in LMIC where the burden of CRDs is increasing fastest, PR is scarce and healthcare services are poorly adapted to deal with such diseases. Although PR is a grade ‘A’ evidence treatment for adults with COPD^12^ and has been used in other chronic lung diseases,^13^ its efficacy in PTBLD is not known. In a development study to examine the impact of PR for people with PTBLD in Uganda, it was feasible to run a PR programme and participants reported clinically important improvements in quality of life, exercise capacity and respiratory outcomes.^14^ To date, there has been little attention to the role of PR in PTBLD globally, particularly in Africa where a significant number of PTB survivors reside.

### Study objectives

The primary objective of this trial is to assess the impact of a 6-week PR programme on maximal exercise capacity using the incremental shuttle walking test (ISWT) among adults living with PTBLD postintervention.

The secondary objectives include assessing the impact of PR on quality of life and other outcomes for patients with PTBLD, and to conduct a cost–benefit analysis of PR.

## Methods

### Study design

This is a prospective, randomised waiting-list controlled trial with blinded outcome measures, comparing PR versus usual care for patients with PTBLD. During this effectiveness trial, a total of 114 participants will be randomised (1:1) to receive either usual care (waiting-list) or PR (figure 1).

**Figure 1 F1:**
[figure not shown]
Figure showing the study flow in the post-TB pulmonary rehabilitation (PR) trial. PTBLD, post-TB lung disease; R&A, recruitment and assessment; TB, tuberculosis.

### Study setting

The study is conducted at the PR centre located at the Makerere University Lung Institute (MLI) Clinic, Kampala, Uganda. The MLI clinic is an academic outpatient clinic within the Mulago National Referral hospital, a teaching and clinical research hospital for Makerere University.

### Study population

#### Recruitment

Adults with PTBLD will be referred from health facilities and clinics (TB treatment centres and HIV/TB caring centres) around Kampala to the PR centre. Existing registers have around 300 adults living with PTBLD and additional patients will be screened directly from the outpatient departments.

In this study, a patient is considered to have PTBLD if they successfully completed treatment for microbiologically confirmed pulmonary TB but continue to experience chronic respiratory symptoms with radiological evidence of lung parenchymal damage.

#### Participant invitation

The process of identifying and inviting eligible patients was refined in the development study. Eligible individuals identified as having an established PTBLD diagnosis will be received at the PR centre at the MLI. Literate participants will be asked to read the patient information sheet (PIS) about the study, written in English or translated in the local language. Illiterate participants will have the contents read to them in full by a study staff, in the presence of a witness who will be present during the whole process. Participants will have the opportunity to discuss the PIS with the study medical personnel. Once the study staff are satisfied that the participant has understood the PIS, and is interested in taking part in the study, they will be taken through the informed consent process. Participants will give consent before undergoing screening tests and procedures, and if still eligible after the screening process, will be taken through another informed consent process for randomisation.

### Eligibility criteria

#### Inclusion criteria

A patient with PTBLD is eligible for the trial if they meet all of the following criteria: aged ≥18 years, willing and able to provide written informed consent (signed or witnessed consent if the patient is illiterate), a documented history of smear positive pulmonary TB with treatment completed ≥6 months prior to study enrolment, a negative Xpert MTB/RIF assay for *Mycobacterium tuberculosis* at the time of study enrolment, and report a Medical Research Council (MRC) dyspnoea grade ≥2.

#### Exclusion criteria

A PTBLD patient is ineligible for the study if they have co-morbidities that preclude exercise (eg, known unstable cardiovascular disease, locomotor difficulties) or if they are unwilling to participate for any reason or had any condition (social or medical) which in the opinion of the investigator would make study participation unsafe.

### Randomisation

Once eligible participants have consented to take part in the study, they will be randomised using a web-based randomisation system (https://www.sealedenvelope.com/). Participants will be randomised (1:1) to receive either usual care or PR. Access to the web-based system will be controlled through an authorised username and password. Randomisations will be conducted by a member of the study team independent from the data collection team and will be revealed to the data collection and intervention delivery teams after baseline measurements have been obtained.

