### PR team

The PR team has received adequate training on the delivery of PR and participated in the development study which informed this trial.^14^ Furthermore, the individuals are registered health professionals (physiotherapist, physicians and nurses) and have undertaken training regarding the study tests, procedures and measurements per protocol as well as Good Clinical Practice.

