### Assessment and follow-up

Participants in both arms of the trial will be asked to attend the baseline, 6-week and 12-week postintervention assessment visits at the PR centre at MLI. Data will be collected by the study staff (medical doctor, nurse and physiotherapist). Table 1 shows all baseline and follow-up assessment data that will be collected during the trial, in accordance with a minimum recommended dataset for PR trials in LMIC.^16^

**Table 1 T1:** The table shows the assessment and follow-up schedule

Observation/Investigation	Screening/baseline assessments	Randomisation	12 weeks of study participation	
			Hospital based pulmonary rehab	Follow-up phase of homebased exercises
			End of 6 weeks of PR	End of 6 weeks of home exercises
Written informed consent	x	x		
Demographics	x	x		
Medical history	x	x		
Clinical exam	x	x		
Chest X-ray	x			
Spirometry		x		
MRC dyspnoea grade	x		x	x
Assess symptoms	x		x	x
Incremental Shuttle Walk Test	x		x	x
Endurance Shuttle Walk Test	x		x	x
Borg breathlessness scale	x		x	x
Mid Upper Arm Circumference	x		x	x
Sit-to-stand time	x		x	x
COPD Assessment Test		x	x	x
Clinical COPD Questionnaire		x	x	x
Patient Health Questionnaire		x	x	x
HADS		x	x	x
WPAI		x	x	x
Physical Activity (Actigraph monitor)		x	x	x
Cost/benefit analysis		x	x	x
EQ-5D-5L Questionnaire		x	x	x

COPD, chronic obstructive pulmonary disease; EQ-5D-5L, European Quality of Life 5-Dimensions; HADS, Hospital Anxiety and Depression Scale; MRC, Medical Research Council; WPAI, Work Productivity and Activity Impairment.

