### Blinding (masking)

Due to the nature of PR, it will not be possible to blind participants to their group allocation but participants will be asked not to reveal their group during the follow-up assessments. The participant and treating clinician will be aware of treatment allocation, however, the outcome measures will be performed by staff blinded to treatment allocation and the ISWT (primary outcome) will be prioritised to reduce the risk of un-blinding. Any episodes of unblinding will be documented and reported.

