#### Incremental Shuttle Walking Test

The ISWT is frequently used as an outcome measure for PR.^24^ Improvement in walking distance of 35 m during the post-PR shuttle test, measured from baseline (pre-PR) using the ISWT is considered a clinically important difference.^18^ The ISWT requires the patient to walk up and down a 10 m course, identified by two cones inset 0.5 m from either end to avoid the need for abrupt changes in direction. The speed at which the patient walks is dictated by an audio signal played on an audio device. Each participant will receive standardised instructions to: ‘Walk at a steady pace, aiming to turn around when you hear the signal. You should continue to walk until you feel that you are unable to maintain the required speed without becoming unduly breathless’.^25^ To ensure the learning effect is accounted for, a practice ISWT will be performed and the participant will receive encouragement from the physiotherapist throughout the test in an effort to increase the distance one can walk. The test is terminated when either (1) the patient indicates that they are unable to continue, (2) if the operator determines that the patient is not fit to continue or (3) the operator assesses that the patient was unable to sustain the speed and cover the distance to the cone prior to the beep sounding.^25^

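### The Randomisation section releases allocation to the data collection team after baseline, which conflicts with the claim that outcomes are measured by blinded staff

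*Protocol article*

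**What the plan says.** All references are to the protocol article.

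- **Randomisation.** A team member independent of data collection carries out the randomisation. The allocations then "will be revealed to the data collection and intervention delivery teams after baseline measurements have been obtained".
- **Blinding (masking).** Participants and treating clinicians know the allocation, but "the outcome measures will be performed by staff blinded to treatment allocation". Three safeguards follow: "participants will be asked not to reveal their group during the follow-up assessments"; "the ISWT (primary outcome) will be prioritised to reduce the risk of un-blinding"; and any unblinding is to be recorded and reported.
- **Study design.** The trial is a "prospective, randomised waiting-list controlled trial with blinded outcome measures". The Methods and analysis part of the abstract makes the same claim.
- **Assessment and follow-up.** For the baseline, 6-week and 12-week visits: "Data will be collected by the study staff (medical doctor, nurse and physiotherapist"). No separate assessor group is named.
- **PR team.** Of those who deliver the programme: "the individuals are registered health professionals (physiotherapist, physicians and nurses"). They are also trained in the study's tests and measurements.
- **Incremental Shuttle Walking Test.** During the test "the participant will receive encouragement from the physiotherapist throughout the test in an effort to increase the distance one can walk". Of the three reasons for ending the test, two are decided by the operator.

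**The concern.** One section tells the data collectors the allocation after baseline, and another says that outcomes are measured by staff who do not know it. Unless these are different people, both statements cannot be followed, and the article does not say that they are different people.

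Participants in a rehabilitation trial know their arm, so blinded assessment is the main protection left for the primary outcome. The ISWT needs it. The distance reached depends on how hard the participant tries, a physiotherapist urges the participant on, and the operator can end the test. A tester who knows the arm could, without meaning to, encourage or stop the two arms differently. Such a bias would enter the 6-week primary comparison directly, and no analysis could remove it once the tests had been done.

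**Working it through.** The plan gives no figure on this point, so the check compares the sections with one another.

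**1. Who learns the allocation, and when?** Under Randomisation, two teams learn it: data collection and intervention delivery. Both learn it once baseline measurement is complete. Withholding it until then, and using an independent randomiser, protects allocation concealment and the baseline values. Neither step protects measurements taken later.

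**2. Who measures the outcomes at 6 and 12 weeks?** Assessment and follow-up deals with the baseline, 6-week and 12-week visits together and gives one description of the data collectors: study staff comprising a doctor, a nurse and a physiotherapist. It does not divide baseline collectors from follow-up assessors. The plain reading is that the same function covers all three visits.

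**3. Do steps 1 and 2 fit the Blinding section?** On that plain reading they do not. Those who collect follow-up data have been told the arm, while the Blinding section says that those who perform the outcome measures have not.

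**4. Do the stated safeguards repair this?**

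| Safeguard in the Blinding section | What it guards against | Does it help if the tester has already been told? |
|---|---|---|
| Participants keep their group to themselves | Disclosure during the visit | No |
| ISWT given priority | Disclosure before the primary test | No |
| Unblinding recorded and reported | Undetected episodes | No; it records but does not prevent |

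**5. Does anything else in the article separate the roles?** No. The PR team section lists the same professions as Assessment and follow-up and says that the team is trained in the study tests. Table 2 places assessments, PR classes and data entry in a single staff-time item. Neither shows that the same people do both jobs, but neither separates them.

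**6. Is the primary test open to tester influence?** In part. Instructions are standardised, pace is set by an audio signal, and there is a practice test. Against that, the physiotherapist encourages throughout. Of the three stopping rules, one is the participant's own decision, one is the operator's view of fitness to continue, and one is the operator's assessment that the participant missed the cone before the beep. The last is anchored to an external signal; the second is not.

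**7. Size.** The documents give no estimate of how far knowledge of the arm shifts an ISWT result, so the bias cannot be calculated.

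**The case against.** The best defence is that no section says outright that the data collection team named under Randomisation performs the follow-up tests. That section is about concealment up to baseline, so its data collectors could be the baseline collectors only, with a separate blinded group testing later. The Blinding section is the specific rule on the subject, and its safeguards would be pointless if testers were simply told the arm. On this view the fault is one loose clause in a condensed article.

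Much of this stands as an account of intent. It does not remove the conflict: the article never describes the separate group, and Assessment and follow-up treats the three visits as one. This is also a contradiction in what is stated, not a detail left to a fuller document.

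A reader might infer more than the text supports:

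- **That assessor blinding has in fact been lost, or that an unblinded design was chosen.** The documents show a rule that would remove blinding if followed. They do not show that it was followed.
- **That the testers and the PR team are the same people.** Matching professions do not establish this.
- **That the encouragement is unscripted.** The article does not say so, and scripted wording would normally sit in a standard operating procedure that is not shown.
- **That the bias has a known size.** One 10 m length of the course is 10/35 = 29% of the 35 m target difference, but nothing in the documents supports a shift of one length or of any other amount. False-positive rates would need both an assumed shift and an SD that the article does not state.

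**Conclusion.** The Randomisation clause is wrong as written. It cannot be reconciled with the Blinding section, or with the descriptions in the abstract and Study design section, unless follow-up testers are a group distinct from the data collection team, and the article describes no such group. Followed literally, it removes assessor blinding at 6 and 12 weeks, including for the primary outcome, in a trial whose participants are unblinded.

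The conclusion rests on reading the data collection team as the staff who collect data at all three visits. That is the natural reading of Assessment and follow-up, but it is an inference. The direction of concern is clear because the ISWT is effort-dependent, encouraged and partly operator-terminated. Its size is unknown. The point should be settled before follow-up testing, since bias of this kind cannot be undone afterwards.

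**What to change.** 1. In Randomisation, remove the data collection team from the clause on release of allocation, so that only the intervention delivery team is told after baseline.
2. In Blinding or in Assessment and follow-up, state that staff who perform the 6- and 12-week outcome measures, the ISWT above all, do not deliver PR to those participants and have no access to allocation, whether in the randomisation system or in the study database.
3. If existing staffing cannot support this separation, withdraw or qualify the blinding claim in the abstract, Study design and Blinding sections, so that readers know how the primary outcome was measured.

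The cost is a change of wording, control of access rights and discipline in the rota. Sample size, power and significance level are untouched. Whether current staffing is enough cannot be told from the article: it gives no headcount, and a single physiotherapist could not both deliver PR to a participant and test that participant blind.

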### Participant timeline

After randomisation, the PR team will explain to participants when the PR sessions will take place. For each individual participant, the hospital based PR programme will last 6 weeks, followed by a follow-up period of 6 weeks of home exercises. Participants in the control arm (waiting-list) of the trial will be informed of the date for their first exercise session in approximately 12–15 weeks. Based on our development study,^15^ we expect to find prolonged and possibly improved effects of PR at follow-up. Our experience indicates that a follow-up period of more than 3 months after the start of the PR programme would be unrealistic in this environment without unacceptable attrition. Study participants will receive compensation for their time and transport.

### PR team

The PR team has received adequate training on the delivery of PR and participated in the development study which informed this trial.^14^ Furthermore, the individuals are registered health professionals (physiotherapist, physicians and nurses) and have undertaken training regarding the study tests, procedures and measurements per protocol as well as Good Clinical Practice.

